#### Secondary outcomes

Because of participant numbers, we will present descriptive analyses of the secondary outcomes.

### Cost related data and analyses

Cost diaries, a reliable and valid tool for determining costs in cost-effectiveness research [51], will be collected at each follow-up assessment. In this study we will test the feasibility of using these diaries.

Direct costs (e.g. general practitioner, physiotherapy, chiropractor, pharmaceutical services) will be calculated using market prices estimated from Medicare Benefits Schedule, worker’s compensation scheme payment schedules and Pharmaceutical Benefits Scheme. Direct healthcare costs (e.g. consumer co-payments) and non-healthcare costs not captured by insurer payments, will be identified. Examples include other professional care, transportation costs and time spent by family members or volunteers providing care.

Indirect costs include lost economic productivity due to the injury. A shadow wage rate will be used to identify opportunity costs of time spent away from work, calculated using income and employment data collected at baseline. Utility weights will be generated using participants’ SF-12 responses, translated to SF-6D utilities [52] using a new Australian algorithm [53]. The resulting cost-effectiveness measure will be cost per QALY saved. *N*-way sensitivity analyses will model second-order uncertainty (e.g. magnitudes of probabilities, treatment effects) where appropriate.

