### Specific objectives

To evaluate feasibility by estimating expected rates of:i.Recruitment (number of patients approached, number consenting to participate, and number eligible to be randomised)ii.Missing data and participant attritionTo test recruitment strategies and develop a model for recruitment to a full trialTo identify relevant factors that could create barriers to subsequent study completion, and develop strategies to overcome theseTo assess the potential effectiveness of pregabalin in reducing pain for patients with acute WAD at risk of poor recovery to determine the adequate sample size for a definitive full-scale effectiveness randomised controlled trial (RCT)To obtain feedback from ED clinicians, local General Practitioners (GPs), trial GPs and patients on their experience with the trial and areas for improvement to inform a full-scale trial

The study will not attempt to provide evidence of clinical effectiveness for pregabalin in people with acute WAD. This is in accordance with the recommendations from the National Institute of Healthcare Research (NIHR) guidelines [33] and the Consolidated Standards of Reporting Trials (CONSORT) for the development of pilot and feasibility studies [34].

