### Sample size

Since this is a feasibility study, a sample size calculation was not performed. We will aim for 30 participants (15 in each arm) as this will be a large enough sample to inform about the practicalities of delivering the intervention in the ED, recruitment, uptake and attrition. The results of this study will inform any necessary post-trial modifications or remodelling prior to implementation of a larger scale multisite RCT.

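### The cost component is there to test diaries, yet the text commits to a cost-per-QALY ratio that 15 patients per arm cannot estimate stably and that N-way analysis cannot give an interval for

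*Protocol article*

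**What the plan says.** The Cost related data and analyses section introduces the cost diaries and gives their purpose: "In this study we will test the feasibility of using these diaries". It then describes a full costing (direct, non-healthcare and productivity costs) and the utilities: "Utility weights will be generated using participants’ SF-12 responses, translated to SF-6D utilities". It names the output: "The resulting cost-effectiveness measure will be cost per QALY saved". On uncertainty it says that N-way "sensitivity analyses will model second-order uncertainty (e.g. magnitudes of probabilities, treatment effects) where appropriate".

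Elsewhere the article sets limits on what the study can show:

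- Specific objectives: "The study will not attempt to provide evidence of clinical effectiveness for pregabalin in people with acute WAD". Cost-effectiveness is not among the listed objectives.
- Sample size: "Since this is a feasibility study, a sample size calculation was not performed". The target is 30 participants, 15 per arm.
- Data analyses, Secondary outcomes: these are to be summarised descriptively, and the reason given is the number of participants. SF-12 is one of them (Study outcome measures).
- Discussion: the study is not powered for the potential effects. The prospect of a cost-effective intervention is tied to the full trial.

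**The concern.** The section gives the cost component one purpose and then promises an output of a different kind. A cost per QALY gained is a comparative quantity, with a between-arm QALY difference in its denominator. The QALYs come from SF-12, which the same article considers too thinly sampled for anything beyond description.

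A ratio is also the summary least suited to a small study. When the denominator is imprecise relative to its size, the estimate can change sign, change quadrant on the cost-effectiveness plane, or become very large, and a negative ratio has no single meaning. The stated treatment of uncertainty does not deal with this. N-way analysis, as usually understood, moves several inputs together over chosen values. Second-order (parameter) uncertainty calls for a joint distribution of the estimates, from a probabilistic analysis or a participant-level bootstrap. A reader of the results would have a point ratio and a set of what-if values, but no measure of how far sampling alone could move the ratio.

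**Working it through.** The plan has no figure to reproduce: it gives no power, SD, effect size, QALY or cost value.

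**Inputs from the article.** 15 per arm, 1:1 allocation (Design overview; Sample size). Follow-up to 12 months.

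**Assumptions, because the article gives none.** 12-month QALY SD 0.10 to 0.20; true QALY gain 0.03 or 0.05; no dropout; unadjusted comparison of means.

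**Step 1: precision from the sample size alone.** SE = SD × √(2/15) = 0.365 SD. With t on 28 df = 2.048, the 95% half-width is 2.048 × 0.365 SD = 0.75 SD. This needs no outside figure. A true QALY gain would have to exceed about three quarters of an SD to be larger than its own half-width.

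**Step 2: QALY difference.**

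| Assumed SD | SE | 95% half-width |
|---|---|---|
| 0.10 | 0.037 | 0.075 |
| 0.20 | 0.073 | 0.150 |

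**Step 3: chance that the estimated difference has the wrong sign,** Φ(−gain/SE).

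| True gain | SD 0.10 | SD 0.20 |
|---|---|---|
| 0.03 | Φ(−0.82) = 0.21 | Φ(−0.41) = 0.34 |
| 0.05 | Φ(−1.37) = 0.09 | Φ(−0.68) = 0.25 |

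Dropout makes this worse. With 12 per arm, SD 0.10 and gain 0.03, the probability rises from 0.21 to 0.23.

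**Step 4: can the ratio have a bounded interval?** A Fieller 95% interval is bounded only if (QALY difference/SE)² exceeds 3.84. Evaluated at the assumed true gains, the values are 0.82² = 0.67 and 0.41² = 0.17 for a gain of 0.03, and 1.37² = 1.88 and 0.68² = 0.47 for 0.05. All fall short. A second grid (SD 0.08 to 0.15, gain 0.02 to 0.05) gave 0.13 to 2.93, again below 3.84 in all nine combinations.

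**Step 5: how far the ratio itself moves.** A simulation of 200,000 draws, normal and uncorrelated, assumed a true extra cost of $500 and a cost SD of $3,000.

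- SD 0.10, gain 0.03, true ratio 500/0.03 ≈ $16,700: the 2.5th to 97.5th percentiles run from about −$281,500 to +$304,900. About 54% of draws show higher cost with a gain, 14% higher cost with a loss, 7% lower cost with a loss and 26% lower cost with a gain (rounded).
- The most favourable combination tried, SD 0.08, gain 0.05, true ratio $10,000: about −$100,900 to +$148,500.

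**For scale.** Detecting a gain of 0.03 with 80% power at two-sided 5% needs 2 × (1.96 + 0.84)² × SD²/0.03² per arm: about 175 for SD 0.10 and 698 for SD 0.20.

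**The case against.** The case on the other side has weight in five places.

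- **Status of the ratio.** It is not a listed outcome or objective, no decision rests on it, and the article already says that the study is not powered. A reader might infer that a headline ratio is planned as early cost-effectiveness evidence. The text does not support that: the Abstract and Discussion tie a cost-effective intervention to the full trial. This limits the consequence but does not remove the commitment.
- **Reading of the section.** The costing paragraphs could describe the method being piloted for the full trial. That is possible, but the text does not say so, and the conditional phrase attaches to the sensitivity analysis, not to the ratio. If deferral was meant, one sentence settles it.
- **Method.** The article does not call its N-way analysis deterministic, and a full protocol or analysis plan could add a bootstrap. The missing detail is therefore not the point. The point is that the article names a method that, as usually understood, does not do what is claimed for it, and a bootstrap would not make the ratio informative at this size.
- **Magnitudes.** QALY SD, gain and costs are all assumed, and baseline adjustment could reduce the SEs. It would be too strong to state flatly that the QALY difference is indistinguishable from zero, since the true effect is unknown. Only the 0.75 SD follows from the article.
- **Scope.** A reader might infer that the study as a whole exists only to test diaries, or that the economic exercise yields nothing. Neither holds. The Specific objectives list several feasibility aims and an assessment of potential effectiveness on pain, and running SF-12 through to SF-6D tests the economic workflow.

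One detail also deserves mention. The Statistical analysis paragraph speaks of models for each outcome, while the Secondary outcomes paragraph says descriptive. The latter is the more specific for SF-12.

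**Conclusion.** The point holds for the cost component. Its stated aim is diary feasibility, and the unconditional cost-per-QALY output goes beyond that aim and beyond the limits that the article sets on effectiveness, power and the analysis of SF-12. The 95% half-width of 0.75 SD rests only on 15 per arm. The half-width of 0.075 to 0.15 QALY and the wrong-sign probability of about 21% to 34% (true gain 0.03), or 9% to 25% (true gain 0.05), rest on an assumed QALY SD of 0.10 to 0.20, no dropout and no covariate adjustment. Over that range the denominator can take either sign, and the named sensitivity analysis does not provide the sampling uncertainty of the ratio. This should be corrected, but it does not touch the primary outcome or any listed outcome.

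**What to change.** State in Cost related data and analyses that cost per QALY is reserved for the full trial. For this study, report diary return and item completion by visit, and mean (SD) cost and SF-6D utility or QALY by arm, as inputs to the design of that trial.

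Outright removal is not the only sound course. If a joint summary is kept, label it exploratory, give incremental net monetary benefit at stated thresholds with a participant-level bootstrap interval, and say that a bootstrap on about 15 per arm is itself fragile. In either case, do not describe N-way analysis as modelling second-order uncertainty.

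The cost is a change of wording and, if the ratio is reserved, less analysis than planned. The study gives up a point ratio that its data cannot support.

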### Monitoring

#### Collecting, assessing, reporting and managing adverse events

The most common side effects of pregabalin are dizziness and sedation; the dose will be titrated as tolerated. Leg oedema can also develop and may require discontinuation. More severe side-effects are rare.

Information about solicited and spontaneously reported adverse events will be sought from all participants during telephone reviews by the trial GP. If a participant reports an adverse event, the trial GP will determine appropriate action, which may include dose alteration or withdrawal. If a serious adverse event (SAE) is identified, the trial GP will forward this information immediately to the Principal Investigator and Data Safety Monitoring Board. All SAEs, suspected adverse reactions and serious unexpected suspected adverse reactions will be recorded immediately in the source documents, and on the adverse event case report form. Each event will be followed until resolution, stabilisation or until it has been determined that the study treatment is not causal. SAEs still ongoing at the end of the study will be followed up to determine final outcome. Any SAE occurring after the study considered to be possibly related to study treatment will be recorded and reported immediately. Compensation to those who suffer harm from trial participation will be provided by the trial sponsor.

### Withdrawals

Participants will be withdrawn if they develop any exclusion criteria or if they choose to do so, without prejudice to current or future management. The follow-up schedule will continue unchanged for all randomised participants unless a participant chooses to withdraw from follow-ups. If participants cannot complete follow-up outcome measures online or on paper, or are lost-to-follow-up and/or are non-compliant with dosing, we will employ phone calls, home visits and/or communication with their GP. Patients who withdraw during dosing will be made aware of the need for weaning from study medication.

### Dissemination

Authorship eligibility guidelines will follow ICMJE guidelines. The final trial dataset will be available to the investigative team and on reasonable request.

## Discussion

Chronic pain and disability following whiplash injuries is an enormous health and economic burden for Australia and other industrialised countries. Current treatments offer only modest benefit. This feasibility study will assess the feasibility and potential effectiveness of an innovative early intervention delivered to ‘high-risk’ individuals in EDs. Feasibility and potential effectiveness data will inform a full trial, which if successful, will provide an effective and cost-effective intervention with immediate clinical applicability for a costly and treatment resistant condition. It will also have implications for early management of other traumatic conditions.

The protocol was developed for an ‘at risk’ population by a team including a physiotherapist, pain specialist, ED clinician researcher, GP, clinical psychologist and biostatistician.

The primary effectiveness measure is neck pain intensity at 3 months from randomisation for this feasibility study. Measuring this at 3, 6 and 12 months will allow assessment of any sustained effect on outcomes. In the feasibility trial described here, the study will not be powered to assess these potential effects, but will allow necessary post-trial modifications that will maximise effectiveness of the trial to be implemented prior to the rollout of a larger scale multisite RCT.

### Strengths

This study has been designed and is being conducted in accordance with the principles of the Declaration of Helsinki (1996), Good Clinical Practice and all applicable regulatory requirements. This will increase validity, participant safety and scientific integrity as well as reduce bias. The Trial Steering Committee, which includes key study investigators, will ensure that study quality is maintained throughout.

### Limitations

Recruiting through EDs means that our cohort of patients will not be entirely representative of the entire population of whiplash patients. However, by recruiting participants through EDs, we will be most likely to enrol participants with greater pain and distress and therefore at higher risk of poor recovery – the very group we aim to target. Data from our current trials [54] would support this, where patients with acute injury recruited from ED reported average higher pain levels (6.2 ± 1.5) compared to those recruited from primary care and advertisement (4.5 ± 1.0). In addition, we aim to reduce central sensitization beginning in the early aftermath of injury, and ED recruitment allows us to recruit patients within hours of MVC.

### Trial status

Protocol version 8 is dated July 2017. Recruitment began on 20 January 2017 and is ongoing. Important protocol modifications (e.g. changes to eligibility criteria, outcomes, analyses) will be communicated to relevant parties (e.g. investigators, Human Research Ethics Committees, trial participants, trial registries, journals, regulators) as needed.

## Abbreviations

AE: adverse event
DASS: Depression, Anxiety and Stress Scale
ED: emergency department
EDIS: emergency department information systems
GCUH: Gold Coast University Hospital
GP: general practice
MVC: motor vehicle crash
NDI: Neck Disability Index
PCS: Pain Catastrophising Scale
PDS: Post-traumatic Stress Diagnostic Scale
SAE: serious adverse event
S-LANSS: Self-report – Leeds Assessment of Neuropathic Symptoms and Signs Pain Scale
WAD: whiplash-associated disorders
